## Abstract

**Background:**

Patient empowerment represents a potent tool for addressing racial, ethnic and socioeconomic disparities in health care, particularly for chronic conditions such as HIV infection that require active patient engagement. This multimodal intervention, developed in concert with HIV patients and clinicians, aims to provide HIV patients with the knowledge, skills, attitudes and tools to become more activated patients.

**Methods/Design:**

Randomized controlled trial of a multimodal intervention designed to activate persons living with HIV. The intervention includes four components: 1) use of a web-enabled hand-held device (Apple iPod Touch) loaded with a Personal Health Record (ePHR) customized for HIV patients; 2) six 90-minute group-based training sessions in use of the device, internet and the ePHR; 3) a pre-visit coaching session; and 4) clinician education regarding how they can support activated patients. Outcome measures include pre- post changes in patient activation measure score (primary outcome), eHealth literacy, patient involvement in decision-making and care, medication adherence, preventive care, and HIV Viral Load.

**Discussion:**

We hypothesize that participants receiving the intervention will show greater improvement in empowerment and the intervention will reduce disparities in study outcomes. Disparities in these measures will be smaller than those in the usual care group. Findings have implications for activating persons living with HIV and for other marginalized groups living with chronic illness.

**Trial registration:**

ClinicalTrials.gov Identifier: NCT02165735, 6/13/2014.

## Background

There are large, potentially avoidable differences in the incidence, prevalence and outcomes of HIV infection [1]. Combination antiretroviral therapy (cART) represents a powerful treatment with the potential to dramatically reduce disparities in morbidity and mortality from HIV. cART has radically altered the course of HIV and transformed it into a chronic disease with a life expectancy similar to adult onset diabetes [2]. Successful management of HIV-infection requires patients to be empowered, (i.e. engaged, informed, collaborative, committed, and tolerant of uncertainty). HIV disease control requires highly individualized cART based on consideration of multiple factors. These include viral genotype, short and long-term side effects and toxicity, dosing frequency, pill burden, potential drug-drug interactions, comorbidities, and most importantly, consideration of patient preferences and values [3]. Viral suppression, (i.e. attainment of undetectable viral loads), requires long-term rates of medication adherence that exceed 95 % [4]. Effective clinical management requires near complete suppression of viral replication in order to restore immune function, minimize viral mutations and drug resistance, prevent opportunistic infections, and decrease risk of transmission of HIV infection to others [4].

Poor and minority patients are less likely to be active partners in their own care [5]. Poor and minority patients, including persons living with HIV (PLWH), report lower partnership levels with their clinicians, [6] miss more office visits, [7] ask fewer questions during their visits, [8–10] report less confidence in self-management,[11] and more frequently miss doses [12] or stop taking their cART [13]. Groups that have been historically disempowered also have lower knowledge of their medications, [14] are less likely to report benefits from cancer screening, [14] and less likely to report involvement in cancer screening decisions [15].

Our intervention, developed and piloted in collaboration with PLWH, clinicians in Federally Qualified Health Centers (FQHCs); Patient-Centered Medical Home and a primary care practice-based research network (PBRN), will address these disparities by focusing on empowerment and information access that are needed to make decisions that reflect patients’ values.

## Study aims and hypotheses

The overarching aim of this project is to assess the impact of a multi-model eHealth group behavioral intervention on patient activation among persons living with HIV. The specific aims and hypotheses are shown in Table 1 below.

**Table 1 Tab1:** Study Aims and Hypotheses

Aim 1: Improve PLWH’s empowerment
H 1.1: We will improve patient activation; decision making ability; and perceived knowledge, comfort, and perceived skills at finding, evaluating, and applying electronic health information to health problems.
H 1.2: We will improve clinicians’ communication skills as perceived by PLWH.
Aim 2: Increase PLWH’s receipt of evidence-based care
H 2.1: We will improve patient confidence in adhering to combination antiretroviral treatment (cART), self-reported adherence to cART, and HIV viral suppression (undetectable viral load).
H 2.2: We will increase receipt of evidence-based clinical preventive services.
Aim 3: Improve PLWH’s health
H 3.1: We will improve mental, social, and overall health
Aim 4: Reduce disparities in PLWH’s empowerment
H 4.1: We will produce the greatest improvement in activation for those with lowest baseline activation.
H 4.2: We will observe comparable improvements by race, ethnicity, and education.

## Methods

### Study design

We will conduct a parallel randomized controlled trial. This design allows us to examine pre- and post-assessments of participants randomized to the intervention (treatment group) compared to participants randomized to usual care (control group). Given our focus on individual patients, the nature of our intervention, including its reliance on training and specific tools, the risk for contamination between participants will be relatively small. Any such contamination will bias results towards the null. We considered other designs including randomizing by practice site (cluster RCT), stepped wedge and staggered enrollment trials, but did not choose these designs due to few clusters, data collection burden, and relatively short funding time frame (3 years).

### Eligibility

To maximize generalizability, we opted for a pragmatic trial that employs broad inclusion criteria of participants.

#### Inclusion criteria

>18 years, confirmed HIV diagnosis, and receiving care within a participating site.

#### Exclusion criteria

Inability to provide informed consent, inability to read and speak English.

### Participant recruitment and enrollment

Patients will be recruited from four participating sites in Rochester NY and from four sites in the New York Metropolitan Area. Most of the Rochester sites are dedicated HIV practices that also provide primary care to some of their patients, while all of the NYC sites are Federally Qualified Health Centers (FHQC) that provide primary care, including HIV care. Clinicians and staff in participating sites will refer interested HIV+ patients to a study research assistant (RA). The RA will meet in a private area and review the study protocol and consent patients.

### Procedures for randomization and allocation

Sequential identification (ID) numbers will be generated by our study biostatistician using computer generated random numbers stratified by site (Rochester or NYC) to minimize potential site variation between groups. Assignments will be concealed in sealed opaque, envelopes that contain the group assignment. Following confirmation of the participant’s eligibility, informed consent, and completion of the baseline assessment (T0), the RA will open the envelope and notify the participant whether they have been assigned to the intervention or usual care group.

### Procedures and timing of data collection

The RA will administer surveys to all participants at three times: T0 (baseline); T1 (8–10 weeks following randomization), and T2, (1–3 days following the patients’ next HIV visit which is using 14–24 weeks after baseline). We have chosen to link the timing of the T2 survey to patients’ HIV visits in order to ensure reliable patient recall of the visit. Most patients have HIV visits every 3–4 months, and their HIV Viral Load is routinely measured at these visits. T3 (>52 weeks following randomization) involves chart abstraction. RAs or participating clinical site staff trained in chart abstraction, who are blinded to treatment allocation, will abstract the data from the EHR. Fidelity checks will be conducted on 10 % of the sample by an RA and/or study coordinator in order to achieve >90 % agreement.

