#### Pre-visit coaching

After participants in the intervention group have completed their last session, the RA will meet with the patient prior to their next office visit with their HIV provider. This one-time individual coaching session is designed to reinforce application of skills learned during the group training. A separate manual and fidelity checklist has been developed for this one-on-one session. Key tasks for the session are summarized below (Table 3).

**Table 3 Tab3:** Key tasks for pre-visit coaching

•Bring iPod/ePHR (reminding the patients to bring their iPod to their patient coaching session and to their subsequent doctor visit).
•Preparation of questions (ensuring that the patient has identified and recorded in their iPod key questions to ask their clinician).
•Application and rehearsal of skills (coaching the patient through role play asking his/her questions.

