### Study outcomes and measures

Our study measures reflect our patients’ choice of outcomes related to empowerment including activation, eHealth literacy, and greater decision-making and involvement in care. These outcomes will be assessed using validated scales with sound psychometric properties and through chart abstraction data. These are summarized below (Table 4).

**Table 4 Tab4:** Study measures, data source, and timing

Construct (Hypothesis)	Measure	Data type source	Collection points
Participant characteristics			
Demographics	Standardized questions	Survey	T0
Computer experience	Standardized questions	Survey	T0
Health history	Standardized questions	Survey	T0
Aim 1 (Empowerment)			
Patient activation (H1.1)	PAM [56, 57]	Scale	T0, T1, T2
Decision making (H1.1)	Decision Self Efficacy Scale [26]	Scale	T0, T1, T2
eHealth Literacy (H1.1)	eHEALS [23, 24]	Scale	T0, T1, T2
Involvement in Care (H1.2)	Perceived Involvement in Care [25]	Scale	T0, T1, T2
Aim 2 (Evidence-based care)			
HIV adherence self-efficacy (H2.1)	ASES [29]	Survey	T0, T1, T2
Adherence to cART (H2.1)	Past week adherence [28]	Survey	T0, T1, T2
HIV viral load <50 (H2.2)	HIV viral loads (both actual level; and whether undetectable or not)	Chart abstraction	T0, T2
Evidenced based preventive care	Cancer screening/immunizations [58]	Chart abstraction	T0, T3
Aim 3 (Health)			
Physical and Mental health/Quality of Life (H3.1)	SF-12 [27]	Scale	T0, T1, T2
Aim 4 (Moderators)			
Low Activation (H4.1)	PAM and eHEALS (<median)	Scales	T0
Minority race/ethnicity (H4.2)	Standardized questions	Survey	T0
Low education (4.2)	Standardized questions	Survey	T0
Clinician patient centeredness	Instrument on Doctor-Patient Communication Skills. [30]	Scale	

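### Follow-up viral load stops at the T2 visit, so it cannot show what follows the coached encounter, although the planned T3 chart abstraction could supply later values

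*Protocol article*

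**What the plan says.** Viral suppression is a named outcome. Hypothesis H2.1 in Table 1 covers confidence in adherence, "self-reported adherence to cART, and HIV viral suppression (undetectable viral load"), and the Aim 2 analysis repeats this. (Table 4 tags the row H2.2; I follow Table 1 and the Aim 2 text.)

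Table 4 describes the measure as "HIV viral loads (both actual level; and whether undetectable or not"), by chart abstraction at T0 and T2. The only row listed at T3 is preventive care.

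The section on procedures and timing of data collection places T2 at "1–3 days following the patients’ next HIV visit which is using 14–24 weeks after baseline". The reason given for the link to the visit is reliable recall of that visit. It adds that visits fall 3–4 months apart for most patients, and that "their HIV Viral Load is routinely measured at these visits". It also states that "T3 (>52 weeks following randomization) involves chart abstraction".

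Under Pre-visit coaching, once the last group session is over, "the RA will meet with the patient prior to their next office visit with their HIV provider". On its purpose: "This one-time individual coaching session is designed to reinforce application of skills learned during the group training". Table 3 lists preparing and rehearsing questions for the clinician and bringing the device to the visit. The Clinician training section prepares clinicians to engage patients who bring the ePHR to a visit.

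Under Usual care, controls receive the device and application only after T3.

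**The concern.** The intervention has four components. Two of them, coaching and clinician training, are aimed at a clinic encounter. Any benefit to suppression that runs through that encounter, such as better adherence or a change in treatment afterwards, needs time after the visit to show in the blood. If the only follow-up sample is drawn at that visit, this pathway contributes nothing to the measured difference between arms.

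The stated reason for the visit link, recall, applies to patients' ratings of the visit. It gives no reason to stop collecting a laboratory value from the chart at that point.

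What is at stake is how H2.1 is read. A small or null difference in suppression at T2 could be reported as the effect of the whole intervention, when it covers effects only up to the T2 visit. Later values that would settle the matter should be in charts that the study already plans to open.

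**Working it through.** No figure in the protocol bears on the timing of viral load, so there is none to reproduce. The detectable effect size in the Power section is not in question here. The check is a timeline built from the protocol's own statements.

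**Step 1: order of events in the intervention arm**

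| Event | Timing | Source |
|---|---|---|
| Group sessions, device, ePHR | start after randomisation | Intervention |
| T1 survey | weeks 8–10 | Procedures and timing |
| Coaching | after the last session, before the next HIV visit; interval not given | Pre-visit coaching |
| HIV visit, viral load routinely drawn | usually weeks 14–24 | Procedures and timing |
| T2 survey | 1–3 days after the visit | Procedures and timing |
| T3 chart abstraction | beyond week 52 | Procedures and timing |
| Controls receive device | after T3 | Usual care |

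**Step 2: what a value drawn at the T2 visit can contain.** Anything that changed pill-taking before the draw can be in it: the group sessions, the device, the ePHR and its reminders, and coaching to the extent that it acted before the visit. T2 falls 14 − 10 = 4 to 24 − 8 = 16 weeks after T1. Anything that begins with the encounter itself cannot be in it, because the sample is taken at that encounter.

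**Step 3: follow-up left unused**

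- T2 at week 14: 52 − 14 = 38 weeks to week 52.
- T2 at week 24: 52 − 24 = 28 weeks to week 52.

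**Step 4: routine values in that interval.** Visits every 3–4 months are about 13 to 17.4 weeks apart.

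| | 17.4-week interval | 13-week interval |
|---|---|---|
| 28 weeks left | 28 / 17.4 = 1.6 | 28 / 13 = 2.2 |
| 38 weeks left | 38 / 17.4 = 2.2 | 38 / 13 = 2.9 |

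A patient on the usual schedule would therefore have at least one viral load after the T2 visit and before week 52.

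**Step 5: is a later comparison still randomised and clean?** Yes, as far as the device is concerned: controls do not have it before T3, so values up to week 52 still compare intervention with usual care.

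**Step 6: width of a late window.** Weeks 36–52 span 52 − 36 = 16 weeks. That is longer than a 13-week visit interval but shorter than a 17.4-week one, so a few patients who keep to schedule, and those who miss visits, would have no value in it.

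**The case against.** The best reply is that T2 does test H2.1. The hypothesis concerns the package, and the Discussion accepts that the elements cannot be separated. The parts closest to pill-taking (the group sessions, the device, and the ePHR with medication reminders) all act before T2. Viral load is secondary, and neither H2.1 nor Table 1 promises durable suppression. All of this stands. It limits the point to one late pathway.

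A second reply is that the timeline is partly inferred. The protocol does not say outright that the T2 visit is the coached visit, or that the T2 value is the one drawn there, and the article gives no abstraction window. This also stands. However, both sections speak of the next HIV visit, and routine measurement at visits is the only source of values described.

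A reader might go further and infer three things that the protocol does not support:

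- **That coaching has no exposure time before the T2 sample.** The interval between coaching and visit is not stated, so coaching may act on adherence beforehand.
- **That the T2 value reflects group training alone.** Device use, ePHR reminders and coaching also precede it.
- **That past-week adherence at T2 is equally blind.** With the survey 1–3 days after the visit, 7 − 3 = 4 to 7 − 1 = 6 of the 7 days do fall before it. Those days can still carry the earlier components.

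Nor does it follow that a late value should replace T2 under H2.1. That would separate suppression in time from the adherence measures tested with it, and some participants would lack a value.

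**Conclusion.** The point holds in a limited form. As Table 4 stands, viral load can show effects up to the T2 visit but not changes in adherence or treatment that follow the coached encounter. The unused follow-up is 28–38 weeks, about 1.6–2.9 routine values per patient on the usual schedule.

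This rests on three assumptions: that the T2 visit is the coached visit, that the T2 value is drawn at that visit, and that visits continue every 3–4 months, which the protocol says of most patients. The first two are likely but not stated.

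How much suppression would change after the visit cannot be judged from the protocol, so the size of any missed effect is unknown. The primary outcome, patient activation, is untouched, and the protocol is not in contradiction with itself on this point. It is a worthwhile, inexpensive improvement to a secondary outcome.

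**What to change.** 1. In Table 4, change the viral load collection points to T0, T2, T3.
2. At T3, abstract every dated viral load from randomisation to week 52 in both arms.
3. Prespecify an additional secondary suppression outcome in one late window, identical in both arms and counted from randomisation; for example, the last value in weeks 36–52. State how participants with no value in the window are handled.
4. Keep T2 as the H2.1 suppression measure, and describe it as covering effects up to the T2 visit.

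The cost is a few more fields in an abstraction that already takes place, and a changed entry in Table 4. The downsides are that some participants will have no value in the late window, and that this outcome is read later than the surveys.

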### Data management and quality control

An RA will enter data into a laptop computer and upload it into the Web-based RedCap database [16]. Invalid responses and outliers (those falling outside of response ranges) will be corrected immediately. Quality reports will be conducted weekly using RedCap analytic tools to assess missing data and rates of invalid responses. All laptops will be fully encrypted and password protected. Files linking participant names with study ID numbers will be stored separately on a secure, password protected server.

### Group facilitator training and fidelity

We have conducted group training of group facilitators for the intervention from Rochester and NYC using combined in-person and webcasts/video tele-conferences. The training focused on key knowledge, skill, and attitudes (KSAs) for trainees to facilitate groups and also provide individual coaching. These KSAs include knowledge of curriculum content including use of the device and ePHR, skills in facilitating adult learning in groups, and enthusiasm and expectation that every learner will succeed. The facilitator training was based on application of the steps specified in the training manual. We used direct observation and video recording to review key skills and practice until the specified behavior could be performed with high fidelity. During the intervention phase, the facilitators will also meet monthly and use fidelity rating check lists to ensure adherence. A national expert in fidelity rating will assist with fidelity training, refinement of the fidelity checklist, and analyses of protocol adherence during training sessions.

### Intervention

The intervention primarily focuses on patient activation. It includes group sessions to teach participants how to use the hand-held device, how to use the electronic patient health record (ePHR), and how to effectively communicate with the patients’ HIV clinician.

#### Group training

Group training, co-learning and sharing is critical to facilitating patient empowerment. While an iPod represents “a hook” to encourage participants to enroll, we explicitly target key *intrinsic motivational factors* (autonomy, competence, and relatedness) as a means for energizing motivation to learn to use and apply empowerment tools and skills, and to encourage attendance, participation (dose) and retention (maintenance) in the intervention. Each of the six 90-min sessions focuses on development of a basic competency within a context that supports patient autonomy, competence and human relationships. Content is integrated (i.e. role playing is mixed with app downloading) to maintain enthusiasm. A training manual appears in the Appendix. Key tasks are summarized below: (Table 2).

**Table 2 Tab2:** Key tasks for group training

•Project overview, value affirmation exercise, and basic use of the device (e.g. turning on and off, password, settings, etc.)
•Basic training in use of ePHR (recap and introduction to features, password, back-up, and importing contacts).
•Advanced training in use of ePHR (reminders, data entry, confirmation of data, To Ask list).
•Communication and use of web sites (training in formulating, prioritizing, asking questions, and bookmarking high quality web sites).
•Communication and health apps (role play challenging situations, using ePHR during visit, and downloading health relevant apps).

#### Hand-held device

For the hand-held device, we selected the Apple iPod Touch® based on its widespread availability and adoption, versatility (number of applications, web-enabled), intuitive interface/usability, relative low cost, no requirement for phone or internet service provider contracts, and its “coolness” factor. The latter is important to promoting initial patient engagement, including new membership *in the technology community*. This helps improve patients’ inclusion in mainstream society which has greater levels of web-access (both cellular and ISP-based).

#### ePHR

We will load each device with our customized ePHR developed for PLWH named *URHealth. URHealth* possesses the following features. 1) Drop down menus for common HIV medications with accompanying pill pictures; 2) Common lab tests with brief, understandable explanations. 3) Ability to set reminders for appointments and medications. 4) Personalized “Prompt list” of potential questions for patient to ask their clinician. These are generated based on patient’s age, date of birth and data the patients enter into their device. For example, if the person is under 26 years old, they will be prompted to ask about the HPV vaccine (unless they have entered dates of receipt). Prompts can be personalized by prioritizing them. They can be augmented using personally relevant questions that participants will be trained to generate for themselves. The app is password-protected, adding an additional layer of security over the iPod itself.

